## 6 Statistical analysis

Primary analysis of the BGSi will be completed on an ITT basis at the 3 month endpoint using mixed effect models. Stratification variables will be incorporated into the model and other potential factors that could affect the results will be determined a priori and considered for inclusion in the models. All treatment effect estimates will be presented with 95% confidence intervals and 5% level of significance will be used. Analysis of secondary outcomes will follow the same analysis model as the primary analysis where possible. Binary outcomes will be analysed using multi-level logistic regression. Exploratory analysis will be conducted to investigate the effect of phenotypes and comorbidities on the outcome.

Where possible missing data will be minimised however a maximum-likelihood multiple imputation approach will be used with a sensitivity comparison of complete case dataset. The planned analysis will be specified in the statistical analysis plan (SAP), any deviations from the analysis plan will be justified and fully documented in the results report.

### 7.1 Power calculation

Evidence from the GREAT trial of cognitive rehabilitation in neurodegenerative disease using the same primary outcome Bangor Goal Setting Interview (BGSi) indicated an effect of approximately 0.8 in a population with dementia. This is likely to be an underestimation of the effect in this study as it is likely that the intervention will be more effective in people without neurodegeneration as seen in the population in the GREAT trial.

Assuming a minimally clinically important difference of 2 points (<https://www.thecopm.ca/faq/>) and a more conservative effect of 0.7 would require SD of the measure to be approximately 2.86. Baseline SD observed in the GREAT trial was 1.74, it is likely that variability in our sample is likely to be larger and therefore we can accommodate an Increase in variability of approximately 65%.

A sample of 88 (44:44) will be required to detect an effect of 0.7 on the BGSi at 3 months with 90% power at a 5% significance level. Incorporating an attrition of 25% will require recruitment and randomisation of 118 participants (59:59).

## 7 STUDY SCHEDULE

### 7.1. Enrolment

Participants will be recruited from the cohorts of patients with long Covid and cognitive impairment seen in the Cognitive Disorders Clinics held at University Hospitals Sussex NHS Trust (PI [name]), University Hospitals Southampton NHS Trust (PI [name]), Greater Manchester Mental Health Trust (PI [name]). They will initially be approached by the local pls or associated researchers working at each study site and informed consent for participation will be obtained.

Where necessary, research sites will also recruit from additional sites, including regional Long-Covid services (hosted by Pennine Care NHS Foundation Trust), the “Research For the Future” research database, GP referrals to the research sites and Pennine Care memory clinics, and from tertiary referrals from other COVID clinics (e.g. respiratory clinics). Additionally, University Hospitals Sussex NHS Foundation Trust will recruit from Sussex Community NHS Foundation Trust. This will allow the research sites better access to the target recruitment population, and a more ethnically and socioeconomically diverse and representative population overall. Referrals will be made by staff in the relevant team to the study team at the relevant research site, who will then commence screening and recruitment. With respect to the “Research for the Future” Database, relevant database procedures and policies will be followed. The “Research for the Future” Database will be able to promote CICERO on their website, newsletter, Facebook, or Twitter. The CICERO recruitment poster(s) will also be available for sites to promote the study in clinic. Other research websites, including [www.bepartofresearch.nihr.ac.uk](http://www.bepartofresearch.nihr.ac.uk) and [www.clinicaltrials.gov](http://www.clinicaltrials.gov), will be used to promote the study and recruit participants.

These additional recruitment sites, including Pennine Care NHS Foundation Trust and Sussex Community NHS Foundation Trust, will be set up as Participant Identification Centres (PIC), using a model Non-Commercial PIC agreement.

Regarding recruitment to the following sub-studies: Healthy controls sub-study, UK normative data for Neotiv sub-study, and Normative data for 4 Mountains Test sub-study. We will promote the study and recruit from participant databases associated with our collaborating research sites, and UCL participant pools. Poster(s) will be available for sites to promote the sub-studies in clinic, and at UCL. Where necessary, these sub-studies, will also be promoted on the “Be part of research” database.

Regarding recruitment to the Cognitive rehabilitation workshop for control group participants (sub-study). All control group participants from Workstream 2 will be invited to participate in this online workshop.

Participants are free to withdraw from the study at any time.

The end of the study is defined as the last research intervention for the last participant.

## **7.2 Randomisation Procedure**

There will be no randomisation procedure for workstream 1

For workstream 2 randomisation will take place once consent and baseline data collection has been completed. Randomisation will be on a 1:1 allocation (intervention:control) via a secure online system hosted by NWOORTH, Bangor University. The system will employ a dynamic adaptive randomisation algorithm. The randomisation will be stratified for centre (London/Sussex/Southampton/Manchester). A member of the research team at UCL will enter the participants details into the web form and perform the randomisation, which will either display directly on screen, if the researcher is unblinded or notification of the randomisation result will be sent to the designated parties to organise ongoing contact.

## **7.3 Unblinding procedure**

There are no blinding requirements in workstream 1.

Due to the nature of the intervention in workstream 2 participants will not be blinded to the allocation they receive. However, every effort will be made to maintain blinding for the researchers collecting data where logistically possible. The Trial Statistician will be blind to allocation until the quantitative analysis, as detailed in the statistical analysis plan (SAP) has been carried out. Once the blinded results have been shared with the study team and the results discussed and interpreted, the unblinded analysis (as detailed in the SAP) such as adherence analysis will be carried out.

#### 7.4 Withdrawal of Subjects

Participants are free to withdraw at any time during the trial without any impact on their future health and care. Participant data collected to the point of withdrawal will be used in the analysis set unless consent for this is specifically withdrawn.

### 8 CONSENT

If prior to their clinic appointments, patients give consent to be contacted about research studies then the initial approach about this study will be made either by the local PI or a member of his research team.

Informed consent will be documented electronically via a secure REDcap weblink.

### 9 ELIGIBILITY CRITERIA

These are the same for both Workstreams 1 and 2. However, Workstream 2 has an additional exclusion criteria contingent on findings from baseline cognitive assessment.

#### 9.1 Inclusion Criteria

- Aged between 30 and 60 years
- Evidence of prior CV19 infection
  - either positive CV19 PCR
  - or positive CV19 antibody test
  - or acute symptoms consistent with the recognised core features of acute CV19 infection and post-acute symptoms consistent with the recognised core features of long Covid
- Cognitive impairment persisting more than three months after the acute CV19 infection, defined in terms of subjective reports of cognitive decline post-infection

#### 9.2 Exclusion Criteria

- Cognitive impairment prior to CV19 infection
- Occurrence of acute neurological disorder, such as stroke or encephalitis, that could give rise to cognitive sequelae
- People who are on any medications that are considered by the study investigators to have significant adverse effects on cognition

- A pre-existing major psychiatric or medical disorder that is considered by the study investigators to have potential to affect cognition
- High alcohol intake
- Recreational drug use
- Loss of mental capacity such that the affected individual is unable to give informed consent
- Participants will not be eligible for Workstream 2 if they do not exhibit significant impairment on baseline cognitive assessments, defined as impairment in two or more cognitive domains, as they will not gain from cognitive rehabilitation.
- Participants with pacemakers or other implanted devices, those with metal foreign bodies (e.g. shrapnel from war injuries) and those who have had certain types of surgery will be excluded from the MRI substudy. Although MRI is not known to affect the unborn child, we will also exclude subjects who may be pregnant just to be on the safe side.

## 10 RECRUITMENT

Patients with cognitive Covid will be recruited prospectively from NHS memory clinics held in Sussex, Southampton and Greater Manchester.

This follows a standard procedure within these clinics. All patients attending clinic are given a form asking about their willingness to be contacted for research. The clinic team keep a record of those that give consent to be contacted.

For those patients who have given consent to be contacted, the research team for this particular study will then provide the study Participant Information Sheet.

Where necessary, research sites will also recruit from additional sites, including regional Long-Covid services (hosted by Pennine Care NHS Foundation Trust), the "Research For the Future" research database, GP referrals to the research sites and Pennine Care memory clinics, and from tertiary referrals from other COVID clinics (e.g. respiratory clinics). Additionally, University Hospitals Sussex NHS Foundation Trust will recruit from Sussex Community NHS Foundation Trust. Overall, this will allow the research sites better access to the target recruitment population, and a more ethnically and socioeconomically diverse and representative population overall. Referrals will be made by staff in the relevant team to the study team at the relevant research site, who will then commence screening and recruitment. With respect to the "Research for the Future" Database, relevant database procedures and policies will be followed. The "Research for the Future" Database will be able to promote CICERO on their website, newsletter, Facebook, or Twitter. The CICERO recruitment poster(s) will also be available for sites to promote the study in clinic. Other research websites, including [www.bepartofresearch.nihr.ac.uk](http://www.bepartofresearch.nihr.ac.uk) and [www.clinicaltrials.gov](http://www.clinicaltrials.gov), will be used to promote the study and recruit participants.

These additional recruitment sites, including Pennine Care NHS Foundation Trust and Sussex Community NHS Foundation Trust, will be set up as Participant Identification Centres (PIC), using a model Non-Commercial PIC agreement.

To further ensure the study encompasses people from minority ethnic backgrounds and varying socioeconomic backgrounds we will adjust our recruitment process to both workstreams taking into account age, sex, gender, and ethnicity such that those groups most

likely to be affected by cognitive Covid are well represented. To facilitate this, the following measures will be implemented:

- Preparation of culturally- and linguistically-appropriate recruitment information
- Community outreach
- Cultivating relationships with clinicians caring for diverse groups of patients with long Covid, particularly community CV19 care coordinators

Participants will be included regardless of proficiency in English. For those less proficient then we will seek to find a professional interpreter, and funding for this will be requested of NIHR.

## 11 PATIENT AND PUBLIC INVOLVEMENT (PPI)

PPI work will be led by [name], PPI lead, working alongside [name], who currently leads the PPI element of the Rare Dementia Impact Project (Brotherhood et al., 2019). The Guidance for Reporting Involvement of Patients and the Public (GRIPP) will be used to comply with high quality standards of documentation and reporting of PPI in this study (Staniszewska et al., 2017). The PPI group for this study will consist of a group of 4 people living with 'cognitive' Covid-19. They will be identified with the help of PPI co-lead [name] through peer support networks and advocacy groups (<https://www.longcovid.org/about>). People will be contacted by email or approached face-to-face and provided with written information about the study and their role in it shall they decide to participate. Meetings will take place remotely by videoconference to facilitate logistics and comfort for participants.

Group meetings will take place every three months until month 6 (when the workstream of the intervention starts) and then will become annual (this schedule will be left open to modification to adjust to the needs of the group). We will collect feedback from the PPI groups in the form of written notes and questionnaires and any feedback or participation that takes place by email. The group will be trained at the start of the study on the method of participation (e.g. how to join by video meeting, what the rules of participation will be, how to provide feedback). The PPI team will be particularly heavily involved in workstream 2, taking part in the processes and procedures of this stream (e.g. deciding on the most important elements of the intervention and best way to administer them) and also in the dissemination of outcomes.

## 12 FUNDING AND SUPPLY OF EQUIPMENT

The study is funded by a competitively awarded research grant to [name] from the National Institute for Health Research, as part of an open call for studies into Long COVID in non-hospitalised individuals. UCL will administer the grant and has a collaboration agreement with the University of Magdeburg, Germany, for usage of their Neotiv app for remote testing of cognitive function. The research grant also funds researchers at the other study sites (University of Bangor, University Hospitals Southampton NHS Trust, Greater Manchester Mental Health NHS Foundation Trust).

## 13 DATA HANDLING AND MANAGEMENT

The study will include the use of both identifiable data, and pseudonymised data from patients with cognitive Covid. Identifiable information will be stored securely on Data Safe Haven with limited access and will not be used for analysis purposes. Participant identifiable

information will be securely accessed by the clinic and research teams, to contact and schedule appointments with participants. Participant data for analysis will be pseudonymised using a code. The decoding key will be stored on Data Safe Haven. Pseudonymised participant data will be recorded electronically on password protected university laptops and on Data Safe Haven. Data from third parties will be securely transferred using the Data Safe Haven file transfer portal. Pseudonymised MRI data will be transferred from the University of Sussex to UCL servers using UCL XNAT (<https://www.ucl.ac.uk/isd/services/research-it/ucl-xnat-service>). Data will be maintained on UCL servers to ensure data security.

[figure not shown]

Figure 2. Data flow diagram

## 14 PEER AND REGULATORY REVIEW

This study has been peer reviewed as part of the NIHR grant application process. The Sponsor has accepted this review as adequate evidence of peer review.

The study was deemed to require regulatory approval from NHS ethics. Each approval will be obtained before the study commences.

## 15 ASSESMENT AND MANAGEMENT OF RISK

There are no major disadvantages or risks associated with participation.

## 16 RECORDING AND REPORTING OF EVENTS AND INCIDENTS

### 16.1 Definitions of Adverse Events

| Term               | Definition                                                                                                  |
|--------------------|-------------------------------------------------------------------------------------------------------------|
| Adverse Event (AE) | Any untoward medical occurrence in a patient or study participant, which does not necessarily have a causal |

Cognitive Impairment in Long Covid: Phenotyping and Rehabilitation (CICERO) EDGE 143067; IRAS 302920; Protocol v1.13; 20/12/2024 30/39

|                                                                                                                                                                                                                                                                                                                                                                                                                                           |                                                                                                                                                                                                                                                                                                                                                                                                     |
|-------------------------------------------------------------------------------------------------------------------------------------------------------------------------------------------------------------------------------------------------------------------------------------------------------------------------------------------------------------------------------------------------------------------------------------------|-----------------------------------------------------------------------------------------------------------------------------------------------------------------------------------------------------------------------------------------------------------------------------------------------------------------------------------------------------------------------------------------------------|
|                                                                                                                                                                                                                                                                                                                                                                                                                                           | relationship with the procedure involved.                                                                                                                                                                                                                                                                                                                                                           |
| Serious Adverse Event (SAE).                                                                                                                                                                                                                                                                                                                                                                                                              | Any adverse event that: 
 
• results in death,
 
• is life-threatening*,
 
• requires hospitalisation or prolongation of existing hospitalisation**,
 
• results in persistent or significant disability or incapacity,
 
 or 
 
• consists of a congenital anomaly or birth defect
 
 |
| 
*A life- threatening event, this refers to an event in which the participant was at risk of death at the time of the event; it does not refer to an event which hypothetically might have caused death if it were more severe.
 
** Hospitalisation is defined as an in-patient admission, regardless of length of stay. Hospitalisation for pre-existing conditions, including elective procedures do not constitute an SAE.
 |                                                                                                                                                                                                                                                                                                                                                                                                     |

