### 967 16.2.3 Expectedness

| Category          | Definition                                                                                                                  |
|-------------------|-----------------------------------------------------------------------------------------------------------------------------|
| Expected   | An adverse event which is consistent with the information about the procedure clearly defined in this protocol .     |
| Unexpected | An adverse event which is not consistent with the information about the procedure clearly defined in this protocol . |

968 \* this includes listed events that are more frequently reported or more severe than previously  
969 reported

970 **16.3 Recording adverse events**

971

972 All adverse events will be recorded in the CRF with clinical symptoms and accompanied with

973 a simple, brief description of the event, including dates as appropriate.

975

976 **16.4 Procedures for recording and reporting Serious Adverse Events**

977 All serious adverse events will be recorded in the medical records and the CRF, and the  
978 sponsor's AE log

979 All SAEs (except those specified in section 16.5 as not requiring reporting to the Sponsor)  
980 must be recorded on a serious adverse event (SAE) form. The CI/PI or designated individual  
981 will complete an SAE form and the form will be preferably emailed to the Sponsor within 5  
982 working days of becoming aware of the event. The Chief or Principal Investigator will  
983 respond to any SAE queries raised by the sponsor as soon as possible.

984 Where the event is unexpected and thought to be related to the procedure this must be  
985 reported by the Investigator to the Health Research Authority within 15 days.

986 | Completed forms for unexpected SAEs must be sent within 5 working days of becoming  
987 aware of the event to the Sponsor

988 **Email forms to**  
[[contact]](mailto:[contact])

989

990

991

992 **Flow Chart for SAE reporting**

993

[figure not shown]

Formatted: Numbering: Continuous

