## 16.5 Serious Adverse Events that do not require reporting

Some particular SAEs may not be reported to the sponsor, for example if they are expected to occur on a regular basis and offer no further new information to the safety profile or are related to the disease area of the participants. They will be reported if the frequency or severity of these events is unusual. These events will continue to be recorded in the CRF.

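### Read literally, the 16.1 footnote lets an unplanned admission for worsening long Covid be classed as non-serious, even if it is judged related to rehabilitation

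*Combined protocol and SAP*

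**What the plan says.** Protocol section 16.1 lists the seriousness criteria. One is that the event "requires hospitalisation or prolongation of existing hospitalisation". A footnote to that criterion defines hospitalisation as any in-patient stay and then adds: "Hospitalisation for pre-existing conditions, including elective procedures do not constitute an SAE". The footnote does not qualify the other criteria, among them death, a threat to life, and an event that "results in persistent or significant disability or incapacity".

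Section 9.1 requires, for both workstreams, "Cognitive impairment persisting more than three months after the acute CV19 infection".

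Section 16.4 sends SAEs to the sponsor on a form within 5 working days, apart from those covered by 16.5. It then says "Where the event is unexpected and thought to be related to the procedure this must be" reported to the Health Research Authority within 15 days.

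Section 16.5 begins "Some particular SAEs may not be reported to the sponsor". Its examples are events that are regularly expected and "offer no further new information to the safety profile or are related to the disease area of the participants". It adds: "They will be reported if the frequency or severity of these events is unusual". It keeps these events in the CRF.

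**The concern.** An SAE definition normally leaves out admissions that were arranged beforehand for a stable condition, because they say nothing about the trial treatment. This footnote goes further. Elective procedures appear only as one included example, so the exclusion also reaches emergency admissions and admissions for deterioration. The condition most obviously pre-existing in this trial is the one under study.

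At stake is whether an admission that an investigator attributes to the programme reaches the sponsor and the Health Research Authority as a serious event. The protocol regards worsening after exertion as relevant enough to measure, since the DSQ-PEM is a secondary outcome (5.2.2.3). Section 7.3 says that participants know their allocation and that data collectors are blinded only where this is practicable. A classification left to discretion could therefore be applied differently in the two arms.

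**Working it through.** The plan gives no figure to reproduce, and the point rests on the text. The only arithmetic is the share of participants to whom the footnote can apply. Entry requires post-Covid cognitive impairment, so the share is 120/120 = 100% of planned recruitment (or 118/118 of the calculated sample size).

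**Step 1: is the admission an SAE?** Take an unplanned admission for worsening long Covid that is not fatal, life-threatening or disabling. Hospitalisation is the only criterion in 16.1 it could meet. Long Covid was present before enrolment, so the footnote removes the admission from that criterion. Nothing in the footnote depends on urgency, on deterioration or on the causality rating.

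**Step 2: would it be expected?** Section 16.2.3 ties expectedness to what the protocol defines about the procedure. Section 15 names no major risk. A relapse admission rated as related would therefore be unexpected, which is the kind of event the 15-day duty is meant for.

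**Step 3: which routes remain?**

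| Event | SAE under 16.1, read literally? | SAE form to sponsor (16.4) | 15-day report (16.4) | What remains in any case |
|---|---|---|---|---|
| Unplanned admission for worsening long Covid, judged related, no other criterion met | No | Not required | Doubtful: the duty sits within the SAE procedures | CRF entry (16.3); ratings of severity, causality, seriousness and expectedness (16.2); adverse event count (SAP 5.4) |
| Same admission, but also life-threatening or disabling | Yes | May be waived as disease-area under 16.5 | Stands if related and unexpected | As above, plus the medical records and the sponsor's log (16.4) |
| Unplanned admission for a new condition unrelated to long Covid | Yes | Required | Depends on causality and expectedness | As above, plus the medical records and the sponsor's log |

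The first row is the gap. The second shows the separate difficulty with 16.5.

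**Step 4: 16.4 against 16.5.** Section 16.4 exempts from the form those SAEs that 16.5 specifies, but 16.5 specifies none and gives only examples. The disease-area ground follows an *or*, so it stands alone, and it has no exception for events judged related to the procedure. Yet 16.4 makes reporting of related, unexpected events mandatory, and its later sentence on forms for unexpected SAEs does not repeat the exception. A related, unexpected, disease-area SAE can thus be due at the Health Research Authority while 16.5 lets it go unreported to the sponsor.

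**Step 5: 16.1 against 16.5.** The footnote says that an admission for a pre-existing condition is not an SAE. Section 16.5 speaks of disease-area SAEs as events that exist but may be exempt from reporting. For a long Covid admission the two sections start from different classifications.

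**The case against.** The strongest reply is that such an event is still seen. All adverse events are recorded in the CRF and rated, including for seriousness and causality, and SAP 5.4 reports the number and proportion of participants with AEs and SAEs. The Client Service Receipt Inventory also collects secondary-care use, and the DSQ-PEM is compared between arms at 3 and 6 months. All of this stands. A reader might infer that these admissions are never counted or escalated; the documents do not support that.

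A reader might also infer that the footnote and 16.5 work together to remove the event. They do not. Section 16.5 governs only events already classed as SAEs, so once the footnote has applied, 16.5 is not reached. Where 16.5 does apply, the SAE is still in the CRF and, under 16.4, in the sponsor's log.

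Nor can it be said that the safeguard in 16.5 cannot work. It responds to unusual frequency *or* severity, and severity can be judged on a single event. The sponsor's log and the central REDCap data offer a means of pooling. What is missing is a threshold, a named person to judge what is unusual, and a list of exempt events. Section 16.5 is also permissive, so an investigator may report anyway.

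Finally, that rehabilitation could provoke relapse is an inference. Section 15 names no major risk, and the sessions include pacing. The inference is reasonable given the DSQ-PEM outcome, but the point does not depend on it: the rule gives the same result for any admission judged related.

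None of these replies answers the first row of the table. The footnote can still turn a related, unplanned admission into a non-serious event.

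**Conclusion.** The point holds, within limits. On a literal reading of 16.1, an unplanned admission for worsening long Covid does not meet the hospitalisation criterion, whatever its causality rating. If no other criterion applies, it is recorded and counted only as a non-serious adverse event, and may escape the SAE form and the 15-day report. Separately, 16.5 permits disease-area SAEs to go unreported to the sponsor even when related to the procedure, in tension with 16.4.

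The footnote can apply to every participant, but the number of admissions affected cannot be estimated because the documents give no admission rate. A reader might infer that the SAE count for long Covid admissions would be zero whatever the true rate. That goes too far, because fatal, life-threatening or disabling events remain SAEs.

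The conclusion assumes that investigators apply the footnote as worded and treat long Covid as pre-existing. Sites that read it as covering planned admissions only would report these events, but the protocol would then be applied differently from site to site.

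**What to change.** 1. In the 16.1 footnote, limit the exclusion to admissions planned before consent for a pre-existing condition that has not worsened. State that unplanned admissions, including those for worsening long Covid, count as SAEs.
2. In 16.5, state that the exemption does not apply to any Workstream 2 SAE judged possibly, probably or definitely related to the procedure (the categories in 16.2.2). Removing the disease-area exemption altogether would go further than is needed.
3. Reconcile 16.1, 16.4 and 16.5 so that each type of event has one classification and one reporting route.

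The cost is a protocol wording amendment and a few more SAE forms in a trial of 120 people. If follow-up is already complete, admissions recorded in the CRF can be reviewed again under the revised footnote and tabulated by arm.
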